#### Exploratory Objective Outcomes

To address this objective, participants will provide a urine cotinine test and complete a subset of key questions from the Global Adult Tobacco Survey, a validated self-report of tobacco consumption and passive smoking [63]. From the cotinine test results, participants will be categorized as either (1) no significant smoke exposure or (2) significant smoke exposure. Cotinine is a metabolite of nicotine and indicates exposure to tobacco products within the past 48 hours. The Global Adult Tobacco Survey is a household survey created as a way to globally monitor adult tobacco use and indirectly measure the impact of tobacco control and prevention initiatives. A subset of questions will be asked about current and past tobacco use (if any) and exposure to secondhand smoke. We will compare the outcome measures described above from our primary and secondary objectives to investigate differences between those categorized as no significant smoke exposure and significant smoke exposure.

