### Data Analysis

#### Power Calculations

Our primary outcome measure is MIP. The power calculation was based on work by Messaggi-Sartor et al [14], who examined the effect of RST on respiratory strength and respiratory complications following subacute stroke and measured MIP as the primary outcome. MIP mean gain was 18.9 (SD 15.1) cm H_2_O in the experimental RST group and the mean MIP change was 9.3 (SD 10.1) cm H_2_O in the control (sham RST) group. With a total of 80 participants (40 in each group) in this study, a 2-sided repeated measures ANOVA comparing 2 treatments across 3-time points, using a pooled SD of 12.8 would detect a difference at power >0.8 (f=0.16, F=3.067, =0.5, =.5). For our secondary objective, the RST effect on lung infections may be even more robust. Messaggi-Sartor et al [14] reported a 70% lower lung infection rate for subjects who completed RST during subacute stroke rehab, compared with subjects allocated to the control group. The number needed to treat to prevent one lung infection event was seven [14]. The effect of RST on respiratory complications for those with chronic stroke is not yet known. Our exploratory objective is to distinguish responses to RST, based on smoking exposure. The primary intent of this objective is to collect data to power a future, larger study. Specifically, baseline function is lower in current smokers without neurological disease, and their tolerated exercise training volume may be reduced. A sample size of 80 will provide an opportunity to evaluate whether smoking influences responses to the exercise interventions.

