### Effects of Smoke Exposure

This research will also contribute novel exploratory information regarding effects of the EP and respiratory training in people with chronic stroke with and without daily cigarette smoke exposure. Smoking is an independent risk factor for stroke that directly increases the relative risk of stroke in a dose-dependent fashion [69]. Smoking induces vascular inflammation and endothelial dysfunction to accelerate the progression of atherosclerosis [70,71]. Secondhand smoke exposure also independently increases both the risk of stroke and obstructive pulmonary disease [72,73] and no level of passive smoke exposure is considered safe [24]. Chronic smoke exposure increases the work of breathing through dynamic hyperinflation and heightened airway resistance, despite an increased inspiratory neural drive, leading to dyspnea and airway clearance dysfunction [74,75]. Despite the negative impacts of smoking on cardiovascular and respiratory health, its impact on poststroke respiratory rehabilitation is poorly understood. Older adults with obstructive lung disease who completed 6 weeks of inspiratory strength training achieved significant improvements in MIP and dyspnea, and reported physical quality of life, yet in contrast to adults without lung disease, no gains in walking endurance occurred. These results suggest that individuals with lung disease recovering from stroke may require additional training time or combinatorial exercises to improve walking [76].

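### Smoke exposure is classified from urine cotinine alone, so smoke-free nicotine or tobacco users, most clearly those who never smoked, would be counted as smoke-exposed

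*Protocol article*

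**What the plan says.** All references are to the Protocol article.

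- **Grouping rule** (Exploratory Objective Outcomes): "From the cotinine test results, participants will be categorized as either (1) no significant smoke exposure or (2) significant smoke exposure".
- **What the marker measures** (same section): "Cotinine is a metabolite of nicotine and indicates exposure to tobacco products within the past 48 hours".
- **What else is collected** (same section, from the Global Adult Tobacco Survey): "A subset of questions will be asked about current and past tobacco use (if any) and exposure to secondhand smoke". No section uses these answers to assign, correct or exclude anyone.
- **Use of the groups** (same section): the outcomes of the primary and secondary objectives are compared to "investigate differences between those categorized as no significant smoke exposure and significant smoke exposure".
- **Intended construct** (Effects of Smoke Exposure): the trial is to inform on "people with chronic stroke with and without daily cigarette smoke exposure". The rationale there concerns what smoke does to vessels and airways, and it includes passive smoking.
- **Status** (Power Calculations): "The primary intent of this objective is to collect data to power a future, larger study". On the numbers available: "A sample size of 80 will provide an opportunity to evaluate whether smoking influences responses to the exercise interventions". No cut-off, expected exposed share, effect size or power is given for this contrast.
- **Eligibility** (exclusion criteria): no criterion concerns nicotine replacement, e-cigarettes or smokeless tobacco.

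**The concern.** The group labels refer to smoke and the test refers to nicotine. Smokeless tobacco is a tobacco product without smoke, and nicotine replacement supplies nicotine without smoke. Either can turn the test positive, and the rule then places the person with smokers and passive smokers. This follows from the article's own description of cotinine.

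The rule is stated outright, so it is not a detail that the article merely leaves to a fuller document. The survey answers that could correct most of the error are already collected, but the text gives them no role in forming the groups.

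At stake is the exploratory comparison of exposed and unexposed participants, and any estimate of whether exposure changes the response to respiratory strength training. The article says these data are meant to help plan a larger study, so a blurred exposed group affects the use it names. Former or intermittent smokers who test negative are a separate matter and not part of this point.

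**Working it through.** **No figure to reproduce.** The article states no number for the smoke-exposure contrast. The check therefore compares the texts and then works out direction and possible size under stated assumptions.

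**Step 1: rule against construct.** The rule uses one input, the cotinine result. By the article's own sentence, that input covers nicotine and tobacco products. The construct is smoke exposure, direct or passive. People with smoke-free nicotine intake lie inside the first set and outside the second. Neither the eligibility criteria nor the survey, as described, removes them from the exposed group.

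**Step 2: effect on the contrast.** Let D be the true exposed-minus-unexposed difference and q the share of cotinine-positive participants with a smoke-free source only. Let k say how far such people respond like the exposed (k = 0 like the unexposed, k = 1 like the exposed). Take the cotinine-negative group as unexposed. Then

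expected contrast = (1-q)·D + q·k·D = D·[1 - q(1-k)].

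With k = 0 this is (1-q)·D. A later study that wants equal power for D, but is planned on the diluted value, would take N larger by 1/(1-q)².

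| q (assumed) | contrast kept, k = 0 | 1/(1-q)² |
|---|---|---|
| 0% | 100% | 1.00 |
| 5% | 95% | 1.11 |
| 10% | 90% | 1.23 |
| 20% | 80% | 1.56 |

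With q = 20% and k = 0.5, the contrast kept is 1 - 0.20 × 0.5 = 90%. With k = 1 there is no dilution at any q.

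**Step 3: size against sampling error.** For scale only, assume 24 of 80 participants are cotinine-positive, an SD of 12.8 cm H2O (from Power Calculations) and D = 9.6 cm H2O. The last figure is 18.9 - 9.3, the training-versus-sham difference in that section, borrowed because no smoke effect is given.

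- Standard error of the exposed-unexposed contrast: 12.8 × √(1/24 + 1/56) = 3.12.
- Shift at q = 10%, k = 0: 0.10 × 9.6 = 0.96, which is 0.96/3.12 = 0.31 standard errors. It involves 0.10 × 24 = 2.4 people.
- For the difference in training response between exposure groups, with equal arms (12 and 12 exposed, 28 and 28 unexposed): 12.8 × √(2/12 + 2/28) = 6.25. A shift of 0.96 is then 0.15 standard errors.

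If the assumptions hold, the bias is systematic but modest beside the noise in 80 participants.

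**The case against.** **Smoking history.** The Background section speaks of smoking history, and Anticipated Findings speaks of survivors with and without a history of exposure. A former smoker on nicotine replacement has that history, and nothing in the rationale says its effects end on quitting. A reader might infer that every smoke-free nicotine user is a false positive. The documents do not support that. The clear case is a person with no smoking history; for former smokers the answer depends on which of the article's framings is meant. This part of the objection stands, and it also means that k = 0 need not hold for them.

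**Unknown share.** The documents give no value for q. If no participant uses smoke-free nicotine, nothing is diluted from this source. This stands.

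**Future sample size.** A reader might infer that the larger study will be oversized by 1/(1-q)². That follows only if it uses a cleaner definition of exposure. If it reuses the cotinine rule, the diluted contrast is the right planning value. The article does not define the later study's rule, so the multiplier is conditional.

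**Small and exploratory.** The shift is a fraction of a standard error in the illustration, and the randomised comparison is untouched. This limits the importance of the point but does not make the rule match its label.

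**Survey already there.** Cotinine and survey are both listed as serving this objective, so a sensitivity grouping is possible. True, but the text assigns participants by cotinine only. That the information is at hand makes the change cheap; it does not make it unnecessary.

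**Conclusion.** The point holds in a limited form. As written, the rule can label people as smoke-exposed who have nicotine or tobacco intake without smoke, most clearly those who never smoked. If they respond like unexposed people, the expected contrast falls to (1-q) of its true value, so 95% to 80% for an assumed q of 5% to 20%. The share is not in the documents and may be zero, and the loss is smaller if these people respond partly like smokers.

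The documents do not show that dilution will occur, by how much, or that the later study will be wrongly sized. The primary MIP comparison is not affected. This is an inexpensive improvement to an exploratory analysis, worth making because the objective exists to inform planning and most of the needed information is already collected.

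**What to change.** Reword the rule in Exploratory Objective Outcomes so that exposure is classified from cotinine together with the survey answers, and settle it before the exposure comparison is run:

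1. Cotinine-positive with reported smoking or passive smoking: smoke-exposed.
2. Cotinine-positive with a smoke-free source as the only one reported: a separate category outside the exposed group. Identify former smokers within it by their reported history, so that the analysis can be read under either framing in the article.
3. Cotinine-positive with no source reported: keep as smoke-exposed on the test result.
4. Report the cotinine-only grouping as a sensitivity analysis.

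For participants still to be enrolled, add one yes/no item on smoke-free nicotine use (replacement, e-cigarettes, smokeless tobacco) at the time of the urine sample. The Results section reports 69 enrolled by July 2024 against a ceiling of 95, so at most 95 - 69 = 26 people were still to come at that date. For those already enrolled, rely on the survey answers. Do not rely on medication records: the article does not say they are collected, and it obtains medical records only after a reported respiratory complication.

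**Cost.** A reworded rule and one question, with no change to randomisation, treatment or the primary analysis. The downsides are partial reliance on self-report, a slightly smaller exposed group, and incomplete information on replacement therapy and e-cigarettes for those already enrolled. The article also does not say whether the chosen survey questions separate smoked from smokeless tobacco; if they do not, the correction for earlier participants will be partial.

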## Introduction

### Background

Stroke is the leading cause of serious long-term disability in the United States [1]. A decrease in stroke mortality (36.9% decrease from 1999 to 2009), has led to a subsequent increase in those living with the consequences of stroke [2]. As such, it impacts the financial status of patients, families, and health care systems [3]. A retrospective study of inpatient stroke care costs from 2000 to 2020 revealed mean hospital costs per stay were US $15,781 (SD US $330) [4]. The mean lifetime cost of ischemic stroke is approximately US $140,048 in the United States, placing stroke among the top 10 most costly conditions among Medicare beneficiaries [5]. Recurrent stroke, cardiac disease, and respiratory complications are the leading causes of mortality in stroke survivors. Given these financial and health costs, there is therefore a critical need to prevent further cardiovascular and cardiorespiratory decline and reduce the incidence of cardiac and respiratory disease and functional disability.

Although stroke sequelae affect numerous body systems, automatic control of resting ventilation is typically spared in the majority of stroke cases, affected only in more severe brainstem strokes. Motor deficits are often the most debilitating to mobility and return to participation in life roles. Motor processing and the voluntary control of muscles of respiration engaged when speaking, upon exertion, coughing, or with exercise may be weakened following damage directly to the cerebral cortex or the descending axonal projections. Consequently, individuals after stroke may exhibit prolonged exercise intolerance, dyspnea, and airway clearance dysfunction. It is upon this conceptual framework we propose that respiratory muscle training is an important component in the rehabilitation of individuals following stroke. The purposes of this study are to (1) evaluate the effect of a combined exercise program (EP) with respiratory strength training (RST) on measures of impairment, activity, and participation; (2) evaluate its ability to maintain prospective respiratory health; and (3) explore the effect smoking history may have on these outcomes.

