## Discussion

### Anticipated Findings

Results from this study will improve our understanding of the additive benefits of respiratory exercises on short and long-term physiologic, functional, and societal gains for these individuals. We hypothesize that the combined RST+EP will be more effective than the EP alone for stroke survivors with and without a smoking exposure history. Specifically, we hypothesize that combined RST+EP will be more effective in restoring poststroke maximal respiratory pressure, in restoring both physical (walking endurance) and respiratory (airway clearance) function, and in restoring poststroke life and social roles. We also hypothesize that RST+EP will be more effective than EP alone in reducing 1-year postintervention incidence of adverse respiratory events.

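### The exploratory smoke-exposure groups rest on a 48-hour cotinine test, so the comparison does not address smoking history, which the Background and Anticipated Findings sections name as the question

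*Protocol article*

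**What the plan says.** Under Exploratory Objective Outcomes, the protocol article collects two things for this objective: a urine cotinine test and selected questions from a tobacco survey. Only the first forms the groups: "From the cotinine test results, participants will be categorized as either (1) no significant smoke exposure or (2) significant smoke exposure". The same paragraph gives the marker's reach: "Cotinine is a metabolite of nicotine and indicates exposure to tobacco products within the past 48 hours". Of the survey it says: "A subset of questions will be asked about current and past tobacco use (if any) and exposure to secondhand smoke". The outcomes of the primary and secondary objectives are then to be compared to "investigate differences between those categorized as no significant smoke exposure and significant smoke exposure". The article states no role for the survey answers in the grouping or in that comparison.

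Two other sections describe the question as one about history. The third purpose in the Background is to "explore the effect smoking history may have on these outcomes". The hypothesis under Anticipated Findings is about "stroke survivors with and without a smoking exposure history".

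**The concern.** A marker that looks back two days cannot separate a never-smoker from someone who smoked for decades and then stopped. If the question is what a smoking history does to outcomes or to training response, the reference group for that question is mixed, and the comparison answers something else.

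What is at stake is limited but specific. Power Calculations says that this objective is mainly there to gather data for powering a larger study. A contrast between mixed groups could mislead the planning of a study about history. The section on Effects of Smoke Exposure also argues partly from chronic effects on airways and vessels, which a 48-hour marker does not measure directly.

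**Working it through.** **Rule against aim.** The article states no exposure prevalence, cotinine cut-off or power for this objective, so there is no figure of its own to reproduce. The check compares the wording used in each section.

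| Section | How exposure is described | Fits a 48-hour marker? |
|---|---|---|
| Background, third purpose | smoking history | No |
| Anticipated Findings, hypothesis | history of smoking exposure | No |
| Abstract, Methods | smoke exposure, no time frame | Yes, if read as current |
| Study Objective and Aims | smoke exposure, including secondhand | Yes, if read as current |
| Power Calculations | smoking exposure, argued from current smokers | Yes |
| Effects of Smoke Exposure | daily exposure, with a rationale that is partly chronic | Daily: yes. Chronic: only in part |
| Conclusion | exposed and nonexposed | Yes, if read as current |

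**Who is placed where.**
- Former smoker with no recent tobacco or secondhand exposure: grouped with never-smokers.
- Intermittent smoker with no exposure in the 48 hours before the test: grouped with never-smokers.
- Either of these with recent exposure: may test positive and be grouped as exposed.
- User of smokeless tobacco only: can be grouped as smoke-exposed, because the article describes the marker as reflecting nicotine and tobacco products in general.

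**Dilution, as an illustration only.** Let D be the true difference between exposed people and never-smokers, q the share of the cotinine-negative group with a history, and r the fraction of D that those people show.

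Observed contrast = D × (1 − q·r). With r = 1 this is D × (1 − q).

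Let h be the share of all participants exposed by history and c the share cotinine-positive, all of the latter assumed truly exposed. Then q = (h − c)/(1 − c), and at r = 1 the share of D retained is (1 − h)/(1 − c). N = 80 comes from the protocol; h and c are assumptions.

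| h | c | History but cotinine-negative | Cotinine-negative group | q | Retained at r = 1 |
|---|---|---|---|---|---|
| 40% | 30% | 32 − 24 = 8 | 56 | 14% | 86% |
| 50% | 20% | 40 − 16 = 24 | 64 | 37.5% | 62.5% |
| 70% | 10% | 56 − 8 = 48 | 72 | 67% | 33% |

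The result also depends on r. In the middle row, r = 0.5 gives 1 − 0.375 × 0.5 = 81% retained, and r = 0 gives no dilution. The range is wide because nothing in the article fixes h, c or r.

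**The case against.** The strongest reply is that the target is current exposure. Most sections that describe this objective say smoke exposure, current smokers or daily exposure, and an objective marker of recent exposure suits those words. On that reading a cotinine-negative former smoker is correctly placed and nothing is diluted. This stands, and it is why rewording the two history statements is an acceptable remedy. It does not remove the mismatch, because one stated purpose and the stated hypothesis are about history.

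A second reply is that the survey is named as serving this objective, and that a condensed article may leave its use in a model to a fuller document. That stands in part: a reader might infer that the trial will ignore the survey, and the article does not say so. But the grouping rule and the comparison built on it are stated, and both use cotinine only.

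A third reply concerns the remedy. Preferring a biomarker to self-report is defensible, and finer groups are small: three groups by two arms in 80 people average 80/6, about 13 per cell. This argues for adding a history analysis beside the cotinine split, not for replacing it.

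**Conclusion.** The point holds as a mismatch between a stated classifier and a stated aim. As written, the exploratory comparison describes recent tobacco exposure and does not address smoking history.

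Three stronger readings are tempting but not supported:
- That all former and intermittent smokers are counted as unexposed. This happens only to those without recent exposure, which for intermittent smokers means the 48 hours before the test.
- That a known part of the effect is lost. The size depends on an assumed share and on how far former smokers respond like exposed people. The article gives neither. Dilution toward zero is itself conditional, since smokeless users in the exposed group and former smokers who respond differently would change its size or form.
- That the trial's main results are affected. The randomised comparisons of MIP and of respiratory complications do not use this grouping.

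The severity is minor: the objective is exploratory, and both the cotinine result and the survey answers are collected, so the history analysis can still be added.

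**What to change.** Keep the cotinine split and label it as the analysis of recent exposure. Before the data are analysed, add an exploratory analysis of history that uses the survey answers and mutually exclusive groups, for example:
1. Currently exposed: cotinine positive, or reporting current smoking or secondhand smoke. People who use only smokeless tobacco are identified from the survey and handled separately.
2. Former smoker without current exposure.
3. Never smoker without current exposure.

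If the cells are too small, use a single ever/never smoking covariate instead. This assumes that the selected survey questions record the type of tobacco product and past smoking in enough detail, which should be checked.

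The alternative is to reword the third purpose in the Background and the hypothesis in Anticipated Findings as recent exposure only.

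The first option needs no new data collection if that check is met. Its costs are small groups in 80 participants, self-reported history, and a currently exposed group that combines active and passive exposure. The second option costs only a change of wording but gives up the history question.
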